#### Multiparameter MRI (liver and pancreas)

A multiparameter MRI scan will be performed on each visit for the nested cohort to measure lipid, iron load and fibrosis in liver and pancreas according to protocols in development at Clinical Research Imaging Centre. The total duration of scan will be approximately 30 min.

#### Cardiovascular analysis

Nested cohort participants will undergo pulse wave analysis at the radial artery using a non-invasive tonometer to measure wave reflection, pulse pressure and derived arterial stiffness with the augmentation index at 75 beats/min and the administration of two puffs of inhaled salbutamol (200 µg each puff) via a spacer device. Transthoracic echocardiography will be performed to measure longitudinal shortening of the myocardium.

#### Pulmonary function testing and gas transfer

Spirometry will be undertaken in accordance with guidance from the British Thoracic Society for the nested cohort group.^22^ All measurement will be made with participants seated. Forced expiratory volume in 1 second (FEV1) and forced vital capacity (FVC) will be recorded as the best of three consistent readings, and compared with the predicted normal values for the participant’s height, age, gender and ethnicity. Flow volume measurements will also be obtained. Lung volumes will be measured using the steady state method.^22^ Gas transfer/diffusion capacity will be measured using the single breath carbon monoxide transfer factor method.^22^

### Cardiopulmonary exercise testing (CPEX)

CPEX testing will be carried out on day 2 of patient assessment at all visits for nested cohort participants. Participants will be asked not to smoke for 8 hours prior to the test, and to abstain from other strenuous exercise on the same day.

Supervised CPEX testing will be conducted following a standardised incremental protocol on a magnetically braked cycle ergometer. Work-load ramp will be determined using a standard formula.^23^ Testing will be continued until symptomatic limitation, volitional termination, failure to maintain required cadence or if other early termination conditions are met.^24^ Breath by breath O_2_ and CO_2_ analysis will be performed using a fully calibrated metabolic cart. Twelve-lead ECG and O_2_ saturations will be monitored continuously in the pre-test, test and recovery phase. Non-invasive blood pressure will be recorded at rest and at 3-minute intervals during test and recovery phase. The anaerobic threshold (AT) will be independently determined by two assessors using the V-slope method.

### Recruitment

All adult patients that meet the inclusion criteria at the participating sites will be recruited where possible. Patients admitted with an elevated serum amylase will be identified and members of the clinical research team will screen these patients for a diagnosis of AP using the *TRAKCare* management system (InterSystems, Massachusetts, USA). Potential participants will be approached by a member of the direct care team to confirm if they are willing to discuss the research with a member of the research team. If the individual agrees, they will be contacted by a member of the research team during their inpatient stay. If potential participants are discharged before they can be approached, they will not be included in the study

#### Inclusion criteria

The following inclusion criteria will apply to all patients:

Confirmed clinical or radiological diagnosis of AP with an elevated serum amylase greater than 300 U/L.For the potential clinical diagnosis of AP an appropriate clinical history based on compatible clinical features, will be required (ie, abdominal pain, nausea and/or vomiting), supported by the finding of elevated serum amylase greater than 300 U/L. For the radiological diagnosis, if applicable, CT and/or ultrasound scan (USS) evidence of AP will be accepted.

#### Exclusion criteria

Patients under 16 years of age.Prisoners.Any patient that lacks capacity to consent.The additional two exclusions below apply only to those patients being considered for the nested cohort study:Patients not able to undergo MRI scanning for technical reasons will be excluded (eg, those with cochlear implants, implanted pacemaker)Patients with a known allergy to salbutamol

Co-enrolment to other research studies, including drug, interventional and long-term follow-up studies, will be permitted if this has been agreed and documented by the Chief Investigators of co-enrolling studies.

### Statistical analysis plan

Full details of the statistical analysis will be documented in the statistical analysis plan developed prior to any analysis. Any deviations from this will be documented. We will present the data descriptively, where data is categorical numbers and percentages will be presented and where data is continuous number, mean, SD, median, 25th centile, 75th centile, min and max will be presented. Annual incidence of type 3 c diabetes will be given as a percentage with an accompanying 95% CI. For the nested cohort we will present the change in fibrosis index over time graphically with accompanying descriptive statistics, and where appropriate include details of the index episode including aetiology, severity and pre-existing medical background as covariates wherever possible. Quality of assessment will be included as a potential confounder.

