**Methods and analysis:**

This is an observational prospective cohort study in a single centre comprising a University hospital with an acute and emergency receiving unit and clinical research facility. Participants will be adult patient admitted with AP. Participants will undergo assessment at recruitment, 3 months and 3 years. At each time point, multiple biochemical and/or physiological assessments to measure cardiovascular, respiratory, liver, renal and cognitive function, diabetes mellitus and quality of life. Recruitment was from 30 November 2017 to 31 May 2020; last follow-up measurements is due on 31 May 2023. The primary outcome measure is the incidence of new-onset type 3c diabetes mellitus during follow-up. Secondary outcome measures include: quality of life analyses (SF-36, Gastrointestinal Quality of Life Index); montreal cognitive assessment; organ system physiological performance; multiomics predictors of AP severity, detection of premature cellular senescence. In a nested cohort within the main cohort, individuals may also consent to multiparameter MRI scan, echocardiography, pulmonary function testing, cardiopulmonary exercise testing and pulse-wave analysis.

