### Measurements

#### Primary endpoint

Overall cohort: to define the incidence of new-onset type 3c DM in patients with AP, compared with the age-matched population of Scotland.Nested cohort: to define the baseline change in pancreatic fibrosis index measured by multiparameter MRI between 3 months and 36 months after recruitment.

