#### Sample size calculation

Overall sample size calculation has been performed to illustrate how well we will be able to estimate the annual incidence of type 3c diabetes in patients with AP with varying sample sizes.^25 26^ The incidence of type 3c DM was chosen for the purposes of establishing a prospective cohort size because it is specific, measurable, clinically relevant and offers a practice-changing opportunity for intervention. With a sample of 323 we would have 80% power to be able to show a difference from the incidence of DM in the general population (6%) if we observed an incidence in the cohort of 10% or greater. Moreover, this sample size will support the evaluation of the secondary endpoints, allowing us to adjust for any confounding factors.

Nested cohort sample size has been calculated to detect the difference in the 3 months to 36 months change in pancreatic fibrosis index between those with AP with MODS and those with AP without MODS based on Banerjee *et al* estimates of fibrosis index using multiparameter MRI.^27^ Based on a sample size of 20 participants per group, using a two-sided two-sample test with a 5% level of significance and 80% power, we would be able to detect an effect size of 0.909 (where the effect size is the absolute difference in means divided by common SD). To allow for potential dropouts in this part of the study (death, withdrawal) a minimum sample size of 25 individuals will be recruited for the nested cohort.

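### The primary diabetes incidence has no single time basis (during follow-up in the abstract, annual in the analysis and sample size), and the 323-participant, 80% power figure cannot fit both

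*Protocol article*

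**What the plan says.** All references are to the protocol article.

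- Abstract, Methods and analysis: "The primary outcome measure is the incidence of new-onset type 3c diabetes mellitus during follow-up". Assessments are at recruitment, 3 months and 3 years.
- Primary endpoint: the aim is "to define the incidence of new-onset type 3c DM in patients with AP, compared with the age-matched population of Scotland". No time unit is given.
- Statistical analysis plan: "Annual incidence of type 3 c diabetes will be given as a percentage with an accompanying 95% CI".
- Sample size calculation, opening sentence: the calculation is meant to show "how well we will be able to estimate the annual incidence of type 3c diabetes in patients with AP with varying sample sizes".
- Sample size calculation, power sentence: 323 participants are credited with 80% power, and the two rates compared are worded as "incidence of DM in the general population (6%) if we observed an incidence in the cohort of 10% or greater". Neither percentage carries a time unit.
- Oral glucose tolerance test: the scheduled tests are at the 3-month and 36-month visits.

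**The concern.** An annual incidence and an incidence over a follow-up of three years are different numbers, about a factor of three apart at these rates. The article uses both descriptions for the same primary quantity and supports it with a power statement that names neither. It does not say how observations at 3 and 36 months become an annual percentage.

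Two things are at stake. First, a power figure belongs to one time scale only, so the stated 80% may not describe the quantity that will be reported. Second, the primary aim is a comparison with the population of Scotland. If the cohort figure and the population figure are on different time scales, the comparison can mislead, even in its direction.

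**Working it through.** **Inputs.** From Sample size calculation: reference 6%, alternative 10%, n = 323, power 80%. From the abstract: three years of follow-up. Assumed: two-sided 5% alpha (stated only for the nested cohort), constant risk over time, no loss, and all 323 free of diabetes at entry.

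**1. Reproducing 323.** One-sample proportion against a fixed reference, normal approximation:

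n = [(1.96·√(p0(1−p0)) + 0.8416·√(p1(1−p1))) / (p1−p0)]²

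With p0 = 0.06 and p1 = 0.10: n = [(0.4655 + 0.2525) / 0.04]² = 322.2, rounded up to 323. Power at 323 is 80.1%. Other variants do not match: one-sided 259, continuity-corrected 347, arcsine 356, Wald with the alternative variance 442. The matching formula has one yes/no outcome per participant and no term for time or person-years.

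**2. If 6% and 10% are annual**, as the opening sentence of the section implies, the formula credits each person with one year, although three are planned.

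- 36-month risks: 1 − 0.94³ = 16.9% and 1 − 0.90³ = 27.1%.
- n for 80% power: [(1.96·√(0.1694·0.8306) + 0.8416·√(0.2710·0.7290)) / 0.1016]² = 119.2, so 120.
- Power with 323: 99.3% by the normal approximation. With 20% loss (258 participants) it is 97.8%, and with 50% loss (162) 89.5%. The article gives no dropout figure for the overall cohort, so these losses are illustrations.
- As a check on a person-year scale: 323 participants give 323 × 3 = 969 person-years, or 323 × (1 + 0.90 + 0.81) = 875 if time stops at onset. Exact Poisson power is 99.1% and 98.7% respectively.

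**3. If 6% and 10% are cumulative over follow-up**, the 80.1% is right for the cumulative proportion, but the quantity promised in the analysis section is another one.

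- Annual equivalents: 1 − 0.94^(1/3) = 2.0% and 1 − 0.90^(1/3) = 3.5%.
- Example: 32 cases among 323 is 9.9% cumulatively (Wilson 95% CI 7.1% to 13.7%). The same 32 cases over 969 person-years are 3.3% a year (exact Poisson 95% CI 2.3% to 4.7%).

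**4. If the scales are mixed.** A cohort with 10% over 36 months, reported as about 3.5% a year and set beside the undated 6%, would appear to lie below the population. On a common cumulative scale it lies above.

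| Meaning of 6% and 10% | Stated 80% | Word 'annual' |
|---|---|---|
| Annual | Wrong (about 99.3% before loss) | Right |
| Cumulative over follow-up | Right | Wrong |

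**The case against.** The best defence is that the two descriptions are compatible: the abstract names the observation window and the analysis section names the unit. Events during follow-up divided by person-time give an annual incidence. As a reading of the wording this is fair, and the abstract does not say 36-month; that period comes only from the visit schedule. But the defence commits the plan to the annual scale, and on that scale the 80% is wrong for three years of follow-up. It moves the inconsistency into the power statement and does not remove it.

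Four further points stand and limit the finding.

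- A reader might infer that the calculation definitely counts one year per person. That holds only if 6% and 10% are annual, and the power sentence does not say so.
- A reader might infer that 323 is too few. Neither consistent reading shows this: power is about 99.3% or 80.1% before loss.
- A reader might infer that the planned confidence interval has the wrong width. The article attaches the interval to the annual incidence and names no method, which may be in the separate analysis plan. Nothing can be said about its width.
- A reader might infer that onset between visits cannot be dated. The Data management section provides for tracking electronic health records, so dated diagnoses may be available.

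The article defers full details to a separate analysis plan. That plan could choose one scale, but the article's own sections would still disagree.

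**Conclusion.** The concern holds as an inconsistency of time basis: the primary quantity and the stated power do not belong together as written. Either the 80% is wrong for an annual rate followed for three years (about 99.3% before loss, 120 participants sufficient for 80%), or annual is the wrong label for what was powered (10% over 36 months is about 3.5% a year). The first error is conservative. The second matters more, because an annualised cohort figure set against an undated 6% could reverse the direction of the primary comparison.

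The sizes rest on constant risk, a two-sided 5% level, no loss unless stated, and all 323 at risk at entry. The last is doubtful: prior diabetes is not among the exclusion criteria, and the glucose testing section expects participants with insulin-dependent diabetes. The inconsistency itself depends on none of these assumptions.

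Severity: should fix. The text does not support a claim that the cohort is underpowered.

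**What to change.** Choose one time basis and use it for the outcome, the population reference, the 10% alternative and the 95% CI in the abstract, Primary endpoint, Statistical analysis plan and Sample size calculation. Then restate the power on that basis. Either choice is workable.

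- **Cumulative incidence over 36 months.** This fits the visit schedule and the form of the calculation. The 6% must first be confirmed as a population incidence over the same period, or replaced by one; the article does not support simply relabelling it. The 80% for 10% against 6% stands only if that check succeeds.
- **Annual rate.** Compute the rate and its interval from person-years, and restate the power: about 99% before loss if 6% and 10% are annual.

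The cost is wording in four places, a check of the source of the 6%, and one recalculation of power. No new data are needed from participants.

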#### Sample size calculation

Overall sample size calculation has been performed to illustrate how well we will be able to estimate the annual incidence of type 3c diabetes in patients with AP with varying sample sizes.^25 26^ The incidence of type 3c DM was chosen for the purposes of establishing a prospective cohort size because it is specific, measurable, clinically relevant and offers a practice-changing opportunity for intervention. With a sample of 323 we would have 80% power to be able to show a difference from the incidence of DM in the general population (6%) if we observed an incidence in the cohort of 10% or greater. Moreover, this sample size will support the evaluation of the secondary endpoints, allowing us to adjust for any confounding factors.

Nested cohort sample size has been calculated to detect the difference in the 3 months to 36 months change in pancreatic fibrosis index between those with AP with MODS and those with AP without MODS based on Banerjee *et al* estimates of fibrosis index using multiparameter MRI.^27^ Based on a sample size of 20 participants per group, using a two-sided two-sample test with a 5% level of significance and 80% power, we would be able to detect an effect size of 0.909 (where the effect size is the absolute difference in means divided by common SD). To allow for potential dropouts in this part of the study (death, withdrawal) a minimum sample size of 25 individuals will be recruited for the nested cohort.

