**Trial registration numbers:**

ClinicalTrials.gov Registry (NCT03342716) and ISRCTN50581876; Pre-results.

Strengths and limitations of this studyProspective cohort study with molecular mechanistic observations.In-depth clinical and physiological annotation of multiomics data.Drop-out rates in long-term prospective acute pancreatitis (AP) studies is largely unknown.Potential participants with severe AP may lack capacity for consent and recruitment may therefore be slower in this group.

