## Introduction

Acute pancreatitis (AP) is an inflammatory disease of the pancreas usually triggered by gallstones or excess alcohol consumption. The incidence of AP ranges from 13 to 45 per 100.00 individuals, is increasing,^1^ and varies between nations. For example, USA, Finland, Scotland and Germany report higher incidences than England and The Netherlands.^2–5^ AP triggers a cascade of inflammatory events causing cell damage and release of damage-associated molecular patterns that trigger inflammation and cytokine release, initiating a systemic inflammatory response resulting in multiple organ dysfunction syndrome (MODS) in one in five individuals. AP-MODS has a 21% fatality rate during the index episode, and overall in-hospital mortality is 5.2% in Scotland.^6 7^ AP is graded into mild, moderate and severe, based on local and systemic determinants of severity as per the most recent AP classifications (Determinant-based Classification^8^ and Revised Atlanta Classification).^9^ Organ failure in AP most commonly affects the respiratory, renal and cardiovascular systems, but can involve any system.^10^ The pattern of organ failure is difficult to predict and a high level of inter-individual variance is seen, regardless of the aetiology. The molecular mechanisms that explain this inter-individual variation in local and systemic inflammatory processes in AP remain unidentified.^11^ Multiomics analysis of serial time course blood samples has defined molecular patterns in human AP, called endotypes, but the precise relevance of these endotypes to clinical and therapeutic decision-making is not yet determined.^12^

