#### Summary of clinical data to be collected

All participants in the overall and nested cohorts will have the following data collected:

Demographic and clinical background information.Information regarding the acute presentation.Organ function assessment at recruitment, 3-month and 36-month follow-up study visit:

Overall cohort:Full peripheral venous blood profiling, including cardiac biomarkers, standard biochemistry profiling, and samples retained for miRNA profiling, cytokines, telomere length, metabolomic profiling, proteomic profiling, transcriptomic profiling, genomic profiling, leucocyte subset analysis by flow cytometry.Biochemical markers of organ function in urine and samples retained.Pancreatic exocrine function test in stool (faecal elastase).Nutritional assessment.Oral glucose tolerance test at 3-month and 36-month follow-up study visit (with the exception of insulin dependent diabetics who will have random blood glucose measured only).12 lead ECG, blood pressure.Peripheral SpO_2_.Sway balance app non-invasive muscle function tests, 6-minute walk test.Self-administered Patient QuestionnaireGastrointestinal Quality of Life Index.SF-12 Quality of Life.Montreal Cognitive Assessment.Nested cohorts:Pulse wave analysis (with salbutamol inhaler); transthoracic echocardiography.Spirometry and gas transfer.Cardiopulmonary exercise (CPEX) testing.Multiparameter MRI assessment of liver and pancreas.

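### The overall cohort's 323 is an uninflated number: it gives 80% power only if all 323 participants are diabetes-free at entry and evaluable

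*Protocol article*

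**What the plan says.** Under Sample size calculation, the protocol article says that type 3c diabetes incidence was chosen in order to set the size of the prospective cohort, and then: "With a sample of 323 we would have 80% power to be able to show a difference from the incidence of DM". The comparison value is a population rate of 6%, and the sentence closes with the condition "if we observed an incidence in the cohort of 10% or greater". No significance level or sidedness is given for this calculation, and no larger recruitment target appears anywhere in the article.

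The next paragraph, on the nested cohort, does add an allowance: "To allow for potential dropouts in this part of the study (death, withdrawal"). Nothing similar is said for the overall cohort.

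Four other places bear on the point:

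- **Primary endpoint.** For the overall cohort it is new-onset type 3c diabetes, so a person who already has diabetes cannot have the event.
- **Inclusion criteria and Exclusion criteria.** Neither list excludes known diabetes.
- **Summary of clinical data to be collected.** The glucose tolerance test is planned "with the exception of insulin dependent diabetics who will have random blood glucose measured only".
- **Strengths and limitations; Introduction.** The authors write that "Drop-out rates in long-term prospective acute pancreatitis (AP) studies is largely unknown", and that "overall in-hospital mortality is 5.2% in Scotland".

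**The concern.** A sample size that comes straight from the formula is the number that must be analysed. If it is also the number recruited, each participant who dies early, is lost without an outcome or already had diabetes takes power below the stated value. The authors recognised this for the nested cohort and did not carry it over to the overall cohort, where follow-up is just as long and where prior diabetes is a further reason for not being at risk.

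The claim at stake is the precision of the main primary endpoint. As printed, a reader will take 80% power as the property of a recruited cohort of 323.

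A smaller point lies in the same sentence. It ties power to the incidence observed. Power is a probability calculated under a given true incidence.

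**Working it through.** **Inputs.** From Sample size calculation: reference rate p0 = 0.06, treated as fixed; alternative p1 = 0.10; power 80%; n = 323. Assumed: two-sided 5%, the level stated for the nested cohort.

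**Step 1: reproduce 323.** One-sample test of a proportion, normal approximation:

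n = [(1.96 × √(p0(1−p0)) + 0.8416 × √(p1(1−p1))) / (p1 − p0)]²

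- √(0.06 × 0.94) = 0.2375, and 1.96 × 0.2375 = 0.4655
- √(0.10 × 0.90) = 0.3000, and 0.8416 × 0.3000 = 0.2525
- (0.4655 + 0.2525) / 0.04 = 17.95, and its square is 322.2, rounded up to **323**

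Power at 323 is 80.1%. Other versions do not give 323: one-sided 259, continuity-corrected 347, variance under the alternative only 442, arcsine 356. So the match supports the assumed test and shows that nothing was added for attrition.

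**Step 2: power when fewer than 323 are at risk and evaluable.** With m such participants:

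power = Φ[(√m × 0.04 − 0.4655) / 0.3000]

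For example, at m = 258: √258 = 16.06; 16.06 × 0.04 = 0.6425; (0.6425 − 0.4655) / 0.3000 = 0.590; Φ(0.590) = 0.722.

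The article gives neither a loss rate nor a prevalence of diabetes, so the shares below are assumptions. The detectable incidence is the p1 that returns 80% power at m, with p0 kept at 6%.

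| Assumed non-evaluable share | m | Power at a true 10% | Incidence detectable with 80% power | Recruits needed to keep 323 |
|---|---|---|---|---|
| 0% | 323 | 80.1% | 10.0% | 323 |
| 5% | 306 | 78.3% | 10.1% | 340 |
| 10% | 290 | 76.4% | 10.2% | 359 |
| 20% | 258 | 72.2% | 10.5% | 404 |
| 28% | about 233 | 68.6% | 10.8% | 449 |

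The 28% row combines 20% loss with 10% prior diabetes: 0.80 × 0.90 = 0.72, and 323 × 0.72 = 232.6. The last column is 323 divided by (1 − share), rounded up. It is shown for scale only.

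**Step 3: what the table assumes.** Each non-evaluable participant is taken to contribute nothing. That is right for people who have diabetes at entry. It is too severe for people lost part-way if their earlier results or linked records are used, so for a given amount of loss the power figures are lower bounds.

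**The case against.** The strongest reply is that nothing has been miscalculated. The printed sentence is true of 323 analysed participants, and the article never says that 323 is the number to be recruited. The section presents the calculation as an illustration over varying sample sizes, and Recruitment takes all eligible adults where possible, with no cap. This stands in part: a reader might infer an arithmetic error, and there is none. But the same section says that the endpoint was used to set the cohort size, and no other target is given. The ambiguity is what needs to be resolved.

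The second reply is that missing a visit does not mean missing the outcome. Data management provides for tracking of health records, Withdrawal of participants lets earlier or routine data be kept, and glucose is also tested at 3 months. This also stands, and is why the figures are lower bounds. It does not help with existing diabetes, since no follow-up can put those people at risk.

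Several stronger readings are tempting and are not supported:

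- *That the nested cohort supplies a 20% dropout rate to borrow.* The text gives 20 per group and then a minimum of 25 individuals for the nested cohort, not 25 per group. A rate of 20% would be the reader's interpretation, and it would concern repeated MRI.
- *That people with existing diabetes will be counted as non-events, pulling the estimate down.* The endpoint is defined as new-onset, and nothing says that they stay in the denominator.
- *That the glucose test exception proves that people with diabetes are enrolled.* It applies at the 3- and 36-month visits, so it would also cover those who became insulin dependent after the episode. The firm evidence is that no exclusion exists.
- *That 5.2% in-hospital mortality is this cohort's death rate.* It is a Scottish figure for all acute pancreatitis, whereas this study excludes patients who lack capacity. Loss of about that size would leave power near 78%.

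**Conclusion.** The point holds as a reporting and planning gap. The 323 carries no slack, and 80% power requires that all 323 be free of diabetes at entry and evaluable for the new-onset endpoint. The article makes no provision for this in the overall cohort, while making one for the nested cohort.

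The size depends on rates that the document does not give. At about 5% non-evaluable the effect is negligible. From about 10% it is a visible overstatement, and at 28% roughly 11 points of power are lost. In terms of detectable incidence the shift is modest, from 10% to at most 10.8% over the range shown. These results rest on the inferred two-sided 5% test, the normal approximation and no contribution from non-evaluable participants.

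A reader might infer that the study is inadequate for its primary endpoint. The document does not support that: every loss rate is assumed, and the planned analysis is a percentage with a 95% confidence interval. The point should be fixed, but the design does not depend on it.

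**What to change.** In Sample size calculation:

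1. Either state that 323 is the number at risk (no diabetes at entry) and evaluable for the primary outcome, or restate power and detectable incidence for the expected at-risk evaluable number. Label any loss and prevalence rates as assumptions and show a range, for example 76% power at 10% non-evaluable and 72% at 20%.
2. State that the primary denominator is participants without diabetes at entry. If partial follow-up or linked records will count towards the outcome, say so, and note that the power figures are then lower bounds.
3. Replace the reference to an observed incidence with the condition that the true incidence is 10%.
4. State the test, the significance level and the sidedness that give 323.

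The cost is a few sentences and slightly less favourable stated figures. No extra patients or assessments are needed.

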### Study design

This is an observational prospective nested cohort study. The overall cohort is the population presenting with AP that meets the eligibility criteria. For the nested cohort of the study, a stratified block design is to be used to recruit equivalent numbers of patients with AP-MODS vs AP without MODS.

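### The nested cohort's recruitment minimum of 25 individuals contradicts its own power calculation, which needs 20 evaluable participants in each of two groups

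*Protocol article*

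**What the plan says.** The second paragraph of Sample size calculation sizes the nested cohort for a comparison of the 3-month to 36-month change in pancreatic fibrosis index "between those with AP with MODS and those with AP without MODS". The basis is given as "Based on a sample size of 20 participants per group", "using a two-sided two-sample test with a 5% level of significance and 80% power", and the result is that "we would be able to detect an effect size of 0.909", defined as a difference in means in units of the common SD.

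The paragraph then turns to death and withdrawal, and says that to allow for them "a minimum sample size of 25 individuals will be recruited for the nested cohort". It gives no dropout rate.

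Study design describes how that cohort is filled: "a stratified block design is to be used to recruit equivalent numbers of patients with AP-MODS vs AP without MODS". Both arms of the comparison therefore sit inside a single nested cohort. Neither 25 per group nor 50 in total appears anywhere in the article.

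**The concern.** A dropout allowance should raise the number recruited above the number needed for analysis. Here the number needed is 2 × 20 = 40 and the number to be recruited is 25. The two sentences stand next to each other and cannot both be right as worded.

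The figure matters because change in fibrosis index is the nested cohort's primary endpoint (Primary endpoint), and this paragraph is the only justification of its size. A team working to the stated minimum could stop at 25 and believe that it had secured 80% power at 0.909 with a margin for loss. It would have neither.

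**Working it through.** **Inputs** (all from Sample size calculation unless noted)
- Evaluable participants: 20 per group, two groups.
- Two-sided 5% level, 80% power.
- Standardised effect d = 0.909, so SD = 1.
- Equal group sizes (Study design).
- Recruitment minimum: 25 individuals for the nested cohort.
- Dropout rate: not stated.

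**Method.** Two-sample t-test. With group sizes n1 and n2, the noncentrality is d × √(n1·n2/(n1+n2)) on n1 + n2 − 2 degrees of freedom, and power comes from the noncentral t distribution.

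**Step 1: reproduce the plan's figure.** For 20 and 20, √(400/40) = 3.162, and 0.909 × 3.162 = 2.875 on 38 degrees of freedom. Power is 79.99%, and the effect detectable at 80% power is 0.9091. The plan's 0.909 is correct. The normal approximation gives 0.886 at this size, so the plan evidently used the t-test.

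**Step 2: compare needed with recruited.** Needed with no loss: 2 × 20 = 40. Recruited at the stated minimum: 25. The shortfall is 15 before any dropout.

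**Step 3: what each size delivers**

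| Evaluable per group | Noncentrality at 0.909 | Power at 0.909 | Detectable effect at 80% power |
|---|---|---|---|
| 20 and 20 (the calculation) | 0.909 × √(400/40) = 2.875 | 80.0% | 0.909 |
| 12 and 13 (25 in total, no loss) | 0.909 × √(156/25) = 2.271 | 58.5% | 1.17 |
| 10 and 10 (25 in total, 20% lost: assumption) | 0.909 × √(100/20) = 2.033 | 48.6% | 1.32 |
| 25 and 25 (50 in total, no loss) | 0.909 × √(625/50) = 3.214 | 88.3% | 0.81 |

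**Step 4: is there a variant under which 25 in total works?** With 12 and 13, the normal approximation gives 62.2% power, and a one-sided 5% t-test gives 71.2%. Neither reaches 80%.

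**Step 5: what the sentence may have meant.** If 20% are lost, 20/(1 − 0.20) = 25 per group, and 40/(1 − 0.20) = 50 in total. So 25 per group is exactly the inflated number for a 20% loss, and after that loss the design returns to 20 per group and 80.0% power. This is an inference from the arithmetic, because the rate is not given.

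**The case against.** **The sentence plainly means 25 per group.** It follows a per-group figure, it is introduced as an upward allowance, and 20/0.80 is exactly 25. This is the likeliest explanation, and if it is right the power claim stands with a 20% margin. But the sentence counts individuals for the nested cohort, and Study design puts both groups in that cohort. A reader has to guess, and the two readings differ by a factor of two.

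**25 is only a minimum.** True: the article never says in total, and more may be recruited. It would therefore be too strong to say that the study will recruit only 25 people or that its power is certainly lost. What stands is that the minimum the plan commits to does not secure the number that its calculation needs.

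**The full protocol may settle it.** The article condenses a full protocol that is not shown and that may word this correctly. However, this is not a detail left out of the article. It is a figure in the article that conflicts with the sentences before it.

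**The nested analysis is largely descriptive.** The Statistical analysis plan section promises graphs and descriptive statistics, and Primary endpoint words the nested endpoint as a change over time without a group contrast. This limits the consequence: one cannot say that a null test result will be misread. Yet the article does claim power for a two-group test, and that claim has to match the number recruited.

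**Conclusion.** The paragraph is wrong as written. The calculation of 20 per group is correct; the recruitment figure attached to it contradicts it. Taken literally, the stated minimum gives about 58% power at 0.909 and a detectable effect of about 1.17 SD with no loss. The 49% and 1.32 SD figures need an assumed 20% loss. That rate is not the plan's own: it emerges only if 25 is read as per group, so applying it to 25 in total is an illustration.

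A reader might go further and argue that even 25 per group fails, because the Introduction says "AP-MODS has a 21% fatality rate during the index episode" and 25 × 0.79 = 19.75. The document does not support this. The 21% describes AP-MODS in general. Nested participants must have capacity to consent (Exclusion criteria), and the article itself notes that patients with severe AP may lack it, so the most severe cases are probably under-represented. The effect would also be negligible. Adding an assumed 90% retention gives 25 × 0.79 × 0.90 ≈ 18 in the MODS group and 25 × 0.90 = 22.5, say 22, in the other. Those sizes still give 79.6% power. No material shortfall is shown on the per-group reading, and no new rule for counting group sizes follows from it.

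**What to change.** The sponsor should confirm which number was intended and correct the sentence.

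- **If 25 per group:** state 25 per group (50 in total: 25 AP-MODS and 25 AP without MODS) and the assumed dropout rate. With 20% loss this returns 20 per group and 80% power at 0.909. The cost is one corrected sentence.
- **If 25 in total:** withdraw the 0.909 statement and restate the detectable effect as about 1.17 SD before dropout, with the value after whatever dropout rate is assumed (1.32 SD if that is 20%). The cost is a less favourable stated effect size.

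Neither repair changes the endpoint, the visits or the analysis.
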